## Abstract

**Background:**

Laparoscopic surgery has been shown to provide important advantages in comparison with open procedures in the treatment of several malignant diseases, such as less perioperative blood loss and faster patient recovery. It also maintains similar results with regard to tumor resection margins and oncological long-term survival. In gastric cancer the role of laparoscopic surgery remains unclear.

Current recommended treatment for gastric cancer consists of radical resection of the stomach, with a free margin of 5 to 6 cm from the tumor, combined with a lymphadenectomy. The extent of the lymphadenectomy is considered a marker for radicality of surgery and quality of care. Therefore, it is imperative that a novel surgical technique, such as minimally invasive total gastrectomy, should be non-inferior with regard to radicality of surgery and lymph node yield.

**Methods/Design:**

The Surgical Techniques, Open versus Minimally invasive gastrectomy After CHemotherapy (STOMACH) study is a randomized, clinical multicenter trial. All adult patients with primary carcinoma of the stomach, in which the tumor is considered surgically resectable (T1-3, N0-1, M0) after neo-adjuvant chemotherapy, are eligible for inclusion and randomization. The primary endpoint is quality of oncological resection, measured by radicality of surgery and number of retrieved lymph nodes. The pathologist is blinded towards patient allocation. Secondary outcomes include patient-reported outcomes measures (PROMs) regarding quality of life, postoperative complications and cost-effectiveness. Based on a non-inferiority model for lymph node yield, with an average lymph node yield of 20, a non-inferiority margin of −4 and a 90% power to detect non-inferiority, a total of 168 patients are to be included.

**Discussion:**

The STOMACH trial is a prospective, multicenter, parallel randomized study to define the optimal surgical strategy in patients with proximal or central gastric cancer after neo-adjuvant therapy: the conventional ‘open’ approach or minimally invasive total gastrectomy.

**Trial registration:**

This trial was registered on 28 April 2014 at Clinicaltrials.gov with the identifier NCT02130726.

## Background

Laparoscopic surgery has been shown to provide important advantages in comparison with an open approach in the treatment of gastrointestinal malignant diseases, such as less perioperative blood loss, faster patient recovery and shorter hospital stay. It also maintains similar outcomes with regard to tumor resection margins and oncological long-term survival [1,2]. In gastric cancer, the role of laparoscopic surgery remains unclear.

The current recommended treatment for gastric cancer consists of radical resection of the stomach, with a free margin of 5 to 6 cm from the tumor, combined with a lymphadenectomy. The extent of the lymphadenectomy, performed according to the guidelines of the Japanese Gastric Cancer Association, is considered a marker for radicality of surgery and quality of care [3]. Therefore, it is imperative that a novel surgical approach such as laparoscopic total gastrectomy should be non-inferior with regard to radicality of surgery and lymph node yield.

Several studies have focused on laparoscopic versus open gastrectomy. These studies are predominantly conducted in Asian countries [4,5], where the incidence of gastric cancer is higher in comparison to Western countries [6,7]. The screening program in Japan, which started in 1983, has enabled important advances in the detection and treatment of early gastric carcinomas in this country [8]. As such, tumor stages are lower at the time of diagnosis compared to Western countries, and it is difficult to translate the results of Asian studies to a population for which no screening program exists, and in which the stages of the tumors at diagnosis are higher [9].

Only a few Western studies, one randomized controlled trial and some cohort analyses, have been conducted comparing laparoscopic and open approaches for gastric cancer [10-14]. In the randomized controlled trial by Huscher *et al*., they found that laparoscopic partial gastrectomy showed similar results to open gastrectomy with regards to quality of oncological resection, as measured by the number of retrieved lymph nodes, and five-year survival rate, whereas patient recovery was faster and admission duration was shorter [10-14]. However, these studies are small and underpowered and are exceeded by changes in neo-adjuvant therapies. Further research is indicated in order to establish the optimal surgical strategy.

Moreover, implementation of neo-adjuvant chemotherapy is currently used after the outcome of different studies on this subject [15,16]. Nowadays the use of neo-adjuvant treatment followed by gastric resection is extensive and applies in stage Ib to IVa gastric cancer [17]. The effect of neo-adjuvant chemotherapy on a laparoscopic gastrectomy in comparison with an open resection remains unclear. For instance, in rectal and breast cancer, neo-adjuvant chemotherapy has been associated with response of the tumor and a lower number of lymph nodes found in the specimen [18]. In gastric cancer, preoperative chemotherapy has been associated with a lower number of tumor-positive lymph nodes, however no difference in total lymph node yield was reported [19]. In other series, laparoscopic gastrectomy has shown non-inferior results with regard to lymph node yield in comparison to open gastrectomy, but these studies were conducted before the implementation of neo-adjuvant chemotherapy [12,20,21]. Moreover, the difficulty of dissection and resection, and the quality of a laparoscopically performed esophagojejunostomy, remains a technical challenge. Considering all these factors, such as the differences in populations, the number of retrieved lymph nodes, the location of lymph nodes in anatomical stations, the increased use of neo-adjuvant chemotherapy and the technical difficulties derived from the laparoscopic total gastrectomy, a randomized controlled trial comparing open and laparoscopic total gastrectomy after neo-adjuvant therapy is warranted. Such a trial could provide an answer to the question, ‘Is a minimally invasive total gastrectomy justified in the era of neo-adjuvant chemotherapy?’.

## Methods/Design

### Study objectives

The objective of this study is to establish the optimal surgical strategy in the treatment of patients with gastric cancer. The STOMACH trial is a prospective, international, multicenter, parallel randomized clinical trial. Patients with gastric cancer selected to undergo a total gastrectomy, who have received neo-adjuvant chemotherapy, are randomized between a conventional ‘open’ and a minimally invasive group.

### Endpoints

The primary endpoint is quality of oncological resection with regard to radicality of surgery and lymph node dissection in all the appointed stations. Both the total number of resected lymph nodes and the resected lymph node stations will be examined. After surgery, the surgeon will attach tags with numbers corresponding with the dissected lymph node stations to the specimen. This will allow for a more extensive assessment of the feasibility of minimally invasive versus open resection.

Secondary endpoints include postoperative complications, which are monitored for 30 days postoperatively. Overall length of hospital stay and Intensive Care Unit (ICU) stay will also be recorded. Survival will be monitored for up to three years postoperatively. Quality of life is assessed with patient-reported outcome measures (PROM), the Euro-Quality of Life-5D (EQ-5D) questionnaire, the European Organizaion for Research and Treatment of Cancer Quality of Life Questionnaire 30 (EORTC-QLQ30 and the Stomach 22 module (STO22). Assessment of quality of life will be performed preoperatively, five days postoperatively, three months, six months and one year postoperatively. Cost-effectiveness will be assessed from a hospital and societal perspective.

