### Power of the study

The number of dissected lymph nodes in gastric cancer surgery is an important marker for radicality of surgery and quality of care [22-24]. Therefore the primary outcome in this study is the number of retrieved lymph nodes in laparoscopic surgery compared to an open procedure.

It is anticipated that laparoscopic gastric resection will show similar surgical resection specimen quality [19], based on the results of the Dutch Cancer Registry (NKR). The sample size calculation is set to achieve 90% power to detect non-inferiority using a one-sided, two-sample t-test. With a margin of non-inferiority at −4.0 and a significance level (α) of 0.05, the sample size requires 66 patients to be included per group, with a total sample size of 132 patients. A non-inferiority margin of −4.0 is deemed feasible, since the current average lymph node yield at the VU University Medical Center ((VUmc) Amsterdam) is around 20, meaning a lymph node yield of 16 is acceptable.

Since lymph node yield is of interest in cases of radical resection, further correction is necessary for radicality of surgery. The NKR showed that a radical resection was achieved in 79% of patients, although palliative resection figures are not given separately. After correction for radicality, a total of 168 patients are to be included. In other, similar prospective studies, no loss to follow-up was recorded, therefore we do not take into account a percentage for loss to follow-up [25,26].

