### Data collection and statistics

Data is collected via a secured Internet module and via datasheets on paper. A secured online module has been especially designed for the STOMACH trial, using OpenClinica, version 3.3. © 2015 OpenClinica, LLC. Paper datasheets, such as completed questionnaires, will be sent to the VUmc by mail, where they are kept in a secured room. Data are collected daily until discharge. PROMs are collected preoperatively, five days postoperatively, at three months, six months and one year postoperatively.

One research fellow in the VUmc will monitor the data of all included patients, and maintain regular contact with all participating centers. All required parameters will be collected in an SPSS data file, SPSS version 22, IBM statistics®, Chicago, Illinois, USA . Data analysis will be performed according to the intention-to-treat principle. Continuous variable will be compared with a T-test or Mann-Whitney U as appropriate, and frequencies will be compared with a chi-square or the McNemar analysis as appropriate.

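### The only test stated for continuous outcomes, a t-test or Mann-Whitney U, makes inefficient use of the preoperative and repeated quality-of-life scores

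*Protocol article*

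**What the plan says.** The Endpoints section of the protocol article lists three questionnaires (EQ-5D, the EORTC core questionnaire and the STO22 module) and their timing: "Assessment of quality of life will be performed preoperatively, five days postoperatively, three months, six months and one year postoperatively". The section on data collection and statistics repeats the schedule: "PROMs are collected preoperatively, five days postoperatively, at three months, six months and one year postoperatively". That makes one score before surgery and four after it.

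The second paragraph of that section gives the analysis methods. "Data analysis will be performed according to the intention-to-treat principle", and then "Continuous variable will be compared with a T-test or Mann-Whitney U as appropriate". Frequencies get a chi-square or McNemar test. No other method for a continuous outcome appears in the article, and this sentence does not single out quality of life.

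The abstract places these measures among the secondary outcomes: "Secondary outcomes include patient-reported outcomes measures (PROMs) regarding quality of life, postoperative complications and cost-effectiveness".

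**The concern.** The design collects a preoperative score and four later scores from the same patients, but the stated tests each compare one number per patient between two groups. A patient's quality of life before surgery usually predicts quality of life afterwards. Removing that predictable part narrows the confidence interval for the difference between arms. The later visits are also correlated with one another, and a two-sample test cannot use that.

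The primary hypothesis is non-inferiority of lymph node yield, so success there shows only that the new technique is not unacceptably worse. Any advantage to patients has to show in secondary outcomes, of which quality of life is one, alongside complications and length of stay. An imprecise analysis makes a real difference easier to miss and leaves a null result harder to interpret.

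**Working it through.** **Inputs from the article.** The assessment times are preoperative, day 5 and months 3, 6 and 12. The trial size is 168, from the section on power: 66 per group, 132 in total, corrected for a 79% radical resection rate. The correction reproduces: 132 / 0.79 = 167.1, which becomes 168, or 84 per arm. This size was set for lymph node yield. No power, effect size or standard deviation is given for quality of life, so there is no planned figure to reproduce.

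**Assumptions, not in the documents.** The correlation r between baseline and follow-up scores is 0.3, 0.5 or 0.7. The variance is the same at baseline and follow-up. For power, the true difference at one visit is 0.4 or 0.5 SD, with two-sided alpha 0.05 and all forms returned.

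**Step 1: variance of the arm difference at one visit**, relative to comparing follow-up scores alone (set to 1). A t-test on change from baseline gives 2(1 − r). Baseline adjustment gives 1 − r². The ratio of the two is 2(1 − r) / (1 − r²) = 2 / (1 + r).

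| r | Change score, 2(1 − r) | Baseline-adjusted, 1 − r² | Cut against follow-up alone | Change score / adjusted |
|---|---|---|---|---|
| 0.3 | 1.40 | 0.91 | 9% | 1.54 |
| 0.5 | 1.00 | 0.75 | 25% | 1.33 |
| 0.7 | 0.60 | 0.51 | 49% | 1.18 |

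Adjustment is the most precise of the three at every r shown. Below r = 0.5 a change score is worse than ignoring the baseline.

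**Step 2: the same gain in patients.** An unadjusted analysis would need 168 / (1 − r²) patients to match the adjusted one: 168 / 0.91 = 185, 168 / 0.75 = 224 and 168 / 0.51 = 329.

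**Step 3: power at one visit.** With 84 per arm, power is Φ(d√(84/2) / √(1 − r²) − 1.96). For d = 0.4 unadjusted, 0.4 × √42 = 2.592, and Φ(2.592 − 1.96) = 73.6%.

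| True difference | Unadjusted | r = 0.3 | r = 0.5 | r = 0.7 |
|---|---|---|---|---|
| 0.4 SD | 73.6% | 77.6% | 84.9% | 95.3% |
| 0.5 SD | 90.0% | 92.5% | 96.3% | 99.5% |

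At 0.4 SD the gain runs from 4.0 to 21.7 percentage points.

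**Step 4: what the repeated visits add.** With complete forms, the gain at a single visit comes essentially from the baseline term. The repeated-measures part matters when some forms are missing, because a patient's observed visits then still contribute, and when a difference is averaged over visits.

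**The case against.** The strongest defence is that the sentence on tests is a generic list in a condensed article. It does not mention quality of life, and it does not say that a separate test is run at each visit or that the baseline is ignored. A t-test on change from baseline would fit the wording and would use the preoperative score. The fuller plan may specify a better model, and the unadjusted test is valid in any case.

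Most of this stands, but it does not remove the point. The article states a method, and a baseline-adjusted repeated-measures model is not among the tests named. The charitable change-score reading is also less precise than adjustment, by a factor of 1.18 to 1.54 in variance at the correlations shown.

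Three stronger readings are tempting but are not supported:

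- **Patients with missing forms are dropped.** A reader might infer this from the named tests. The article promises intention-to-treat and is silent on missing questionnaires, a matter commonly left to the full plan.
- **The comparison is biased.** Randomisation keeps the unadjusted test valid, and its error rate already allows for chance imbalance at baseline. Bias from missing forms would need a pattern of non-response on which the documents give nothing.
- **Many separate tests inflate false positives.** Three instruments at four visits make 12 comparisons, and 1 − 0.95^12 = 46%. That figure assumes independent tests, whereas visits are correlated. A mixed model with an arm difference at each visit leaves the same number of comparisons, so multiplicity is no argument for this change.

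**Conclusion.** The point holds as one of efficiency. For scores taken once before and four times after surgery, the stated t-test or Mann-Whitney U is a valid but weaker choice than baseline adjustment in a repeated-measures model. The loss is modest at r = 0.3 (9% of variance, 4 power points at 0.4 SD) and substantial at r = 0.7 (49%, about 22 points). Its actual size depends on a correlation that the documents do not report. The variance formulas apply to comparisons of means. They do not carry over exactly to the Mann-Whitney test, which likewise takes no covariate.

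A reader might infer that the quality-of-life results would be wrong or the main trial conclusion weakened. Neither follows: the outcome is secondary, and the lymph-node comparison does not depend on it.

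**What to change.** In the section on data collection and statistics, keep the generic test list for single-measurement outcomes and add a statement for quality of life along these lines: each scale will be analysed with a linear mixed model for repeated measures over day 5 and months 3, 6 and 12, with terms for baseline score, arm, visit and arm-by-visit; adjusted mean differences will be reported with confidence intervals. Any t or Mann-Whitney comparison of these scores would then be descriptive.

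Add two clarifications. The model uses all observed postoperative visits and relies on forms being missing at random. It does not resolve death: left alone, it would estimate as though patients who died still had scores. The number and timing of deaths by arm should therefore be reported separately and not treated as ordinary missing forms.

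If a fuller plan already specifies such a model, it is enough to bring the two texts into line. The cost is a few sentences, with no new data, visits or patients. The change should be made before outcome data are examined by arm.

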### Power of the study

The number of dissected lymph nodes in gastric cancer surgery is an important marker for radicality of surgery and quality of care [22-24]. Therefore the primary outcome in this study is the number of retrieved lymph nodes in laparoscopic surgery compared to an open procedure.

It is anticipated that laparoscopic gastric resection will show similar surgical resection specimen quality [19], based on the results of the Dutch Cancer Registry (NKR). The sample size calculation is set to achieve 90% power to detect non-inferiority using a one-sided, two-sample t-test. With a margin of non-inferiority at −4.0 and a significance level (α) of 0.05, the sample size requires 66 patients to be included per group, with a total sample size of 132 patients. A non-inferiority margin of −4.0 is deemed feasible, since the current average lymph node yield at the VU University Medical Center ((VUmc) Amsterdam) is around 20, meaning a lymph node yield of 16 is acceptable.

Since lymph node yield is of interest in cases of radical resection, further correction is necessary for radicality of surgery. The NKR showed that a radical resection was achieved in 79% of patients, although palliative resection figures are not given separately. After correction for radicality, a total of 168 patients are to be included. In other, similar prospective studies, no loss to follow-up was recorded, therefore we do not take into account a percentage for loss to follow-up [25,26].

### Inclusion criteria

All adult patients with primary carcinoma of the stomach, where the tumor is considered surgically resectable (T1-3, N0-1, M0) after neo-adjuvant chemotherapy, are eligible. Only patients with an indication for total gastrectomy are included, in order to exclude bias due to different surgical approaches. Written informed consent is obligatory.

### Exclusion criteria

Exclusion criteria are previous surgery of the stomach and patients with a previous history of cancer or presenting with a co-existing cancer. To allow for appropriate inclusion and randomization, patients operated in an acute setting are excluded. Patients with an American Society of Anesthesiologists (ASA) classification of four of higher are excluded.

### Participating surgeons and clinics

Complication rate, duration of operation and morbidity can be a result of the learning curve of the operating surgeon, and this might bias results. In order to prevent surgeon bias, participating surgeons are to have sufficient experience in open and minimally invasive total gastrectomy. Based on the literature and the Dutch guidelines for gastric carcinoma [27,28], it is required that the participating surgeon has performed at least 20 open and minimally invasive total gastrectomies.

All surgeons in participating centers have sufficient prior experience with both open and minimally invasive gastrectomy. Eight European academic and non-academic centers will participate in the study: the VU University Medical Center, Amsterdam; Academisch Medisch Centrum, Amsterdam; Antoni van Leeuwenhoek Ziekenhuis, Amsterdam; Universitätsklinikum Carl Gustav Carus, Dresden; Hospital Universitario del Sureste, Madrid; Hospital General de Jerez de la Frontera, Cadiz; Salford Royal NHS Foundation Trust, Manchester and Hospital Universitario Basurto, Bilbao.

### Randomization and blinding

Information regarding the study will be provided to the patient at the outpatient clinic. When informed consent is obtained, the patient will be randomized at the outpatient clinic. Randomization occurs via an online module. The participating surgeon can login via a secured module on the STOMACH trial website. Upon filling out the randomization form, an immediate response is obtained, containing a code number and the allocated type of operation.

The study design is unblinded with regard to patient and physician. The patient will be informed about the type of procedure they are allocated to. When patients do not agree to participate in the study they will receive the standard treatment in the corresponding department. The pathologist assessing the specimen is blinded for the operating technique, since radicality of surgery and the number of assessed lymph nodes and lymph node stations is the primary outcome in this trial.

### Data collection and statistics

Data is collected via a secured Internet module and via datasheets on paper. A secured online module has been especially designed for the STOMACH trial, using OpenClinica, version 3.3. © 2015 OpenClinica, LLC. Paper datasheets, such as completed questionnaires, will be sent to the VUmc by mail, where they are kept in a secured room. Data are collected daily until discharge. PROMs are collected preoperatively, five days postoperatively, at three months, six months and one year postoperatively.

One research fellow in the VUmc will monitor the data of all included patients, and maintain regular contact with all participating centers. All required parameters will be collected in an SPSS data file, SPSS version 22, IBM statistics®, Chicago, Illinois, USA . Data analysis will be performed according to the intention-to-treat principle. Continuous variable will be compared with a T-test or Mann-Whitney U as appropriate, and frequencies will be compared with a chi-square or the McNemar analysis as appropriate.

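### Node yield from eight centres is to be compared without a centre term, so any between-centre variation stays in the error term and precision may be given up

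*Protocol article*

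**What the plan says.** Under Data collection and statistics, the article gives one rule for all continuous outcomes: "Continuous variable will be compared with a T-test or Mann-Whitney U as appropriate". No covariate or centre factor is named.

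Power of the study is consistent with that rule: "The sample size calculation is set to achieve 90% power to detect non-inferiority using a one-sided, two-sample t-test". The margin and error rate follow ("With a margin of non-inferiority at −4.0 and a significance level (α) of 0.05"), and then the result: "the sample size requires 66 patients to be included per group, with a total sample size of 132 patients". Neither the standard deviation nor its source is given. The 132 is raised to 168 because the national registry showed 79% radical resections.

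Under Participating surgeons and clinics: "Eight European academic and non-academic centers will participate in the study". The hospitals listed are in the Netherlands, Germany, Spain and the United Kingdom.

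**The concern.** A node count reflects how far the surgeon dissects and how thoroughly the pathologist searches the specimen. Surgeons and pathologists belong to hospitals, so mean yield may differ from one hospital to the next whichever operation is done. A two-sample t-test treats such differences as patient-level noise. A model with a centre term removes them from the error.

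What is at stake is precision. The non-inferiority conclusion depends on how far the lower confidence limit lies from −4, and a wider interval makes a truly non-inferior operation harder to confirm. The plan makes no allowance for loss to follow-up, so the calculation holds no spare patients for a larger spread than planned.

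**Working it through.** **Inputs from Power of the study.** Margin 4 nodes, one-sided α 0.05, power 90%, 66 per group, correction for 79% radical resections. The true difference is taken as 0.

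**Inputs not in the article.** The standard deviation (SD), and the share *s* of total variance that lies between centres. I assume *s* = 5%, 10% and 20%.

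**Step 1: the plan's own figures.** With no SD stated, 66 per group cannot be reproduced independently, only solved backwards. The normal approximation gives SD = 4 × √(66/2) / (1.645 + 1.282) = 7.85; the exact t-test gives 7.76 to 7.81. I use 7.8. Check: standard error = 7.8 × √(2/66) = 1.358; 4/1.358 = 2.946; noncentral t on 130 df, critical value 1.657, power 90.1%. The inflation step reproduces: 66/0.79 = 83.5, rounded up to 84 per group, 168 in total.

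**Step 2, case A: 7.8 is a total SD.** The unadjusted test has 90.1% power whatever *s* is. With centre in the model and arms balanced within centre, the residual SD is 7.8 × √(1 − *s*) on 132 − 9 = 123 df.

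**Step 3, case B: 7.8 is a within-centre SD.** The unadjusted test then faces a total SD of 7.8/√(1 − *s*). With centre in the model and arms balanced, the residual SD is 7.8 and power is 90.1% at every *s*.

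| Centre share *s* | A: residual SD | A: unadjusted power | A: adjusted power | B: total SD | B: unadjusted power | B: adjusted power |
|---|---|---|---|---|---|---|
| 5% | 7.60 | 90.1% | 91.3% | 8.00 | 88.7% | 90.1% |
| 10% | 7.40 | 90.1% | 92.6% | 8.22 | 87.2% | 90.1% |
| 20% | 6.98 | 90.1% | 94.9% | 8.72 | 83.6% | 90.1% |

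In case B, regaining 90% without adjustment would take 70, 74 or 83 per group, which is 178, 188 or 212 in total after the 79% correction.

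**Step 4: arms not balanced within centre.** The adjusted columns above assume balance. In simulation (132 patients, eight equal centres, 8,000 runs per setting, total SD 7.8, allocation ignoring centre):

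| Centre share | Unadjusted power | Adjusted power |
|---|---|---|
| 0% | 90.0% | 88.7% |
| 5% | 90.1% | 89.7% |
| 10% | 90.1% | 90.7% |
| 20% | 90.3% | 93.7% |

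These are the case A results. They show a cost of about 1 point if centres do not differ (1 to 2 across repeat simulations), nothing gained at 5%, and about 1 to 3 points gained at 10% to 20%.

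In case B the adjusted model does not depend on the centre effects, so its power stays at the first-row value, about 88% to 89%. Against unadjusted values of 89%, 87% and 84%, that recovers nothing at 5%, 1 to 2 points at 10% and 4 to 5 points at 20%.

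**Step 5: part of the gain comes from balance.** With centre-balanced allocation, the unadjusted test itself had simulated case A power of 90.9%, 90.9% and 92.6% at 5%, 10% and 20%. Some of the rise in the first table is therefore due to balancing.

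**Step 6: type I error.** At a true difference of −4, the unadjusted test rejected in 4.7% to 5.2% of runs under allocation ignoring centre, and in 3.6% to 5.1% under centre-balanced allocation. It is not inflated. In the balanced case it becomes conservative as the centre share grows.

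**The case against.** The strongest objection is that the article shows no loss of power. It gives neither the SD nor its source. It draws on the national registry for other planning inputs, so the SD could equally come from many hospitals and already contain between-centre variation. The planned 90% then stands. This is right: a shortfall against 90% is conditional.

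The centre share is also assumed. No yields by centre are given, and the article requires surgeons to have a minimum experience in both operations, which may narrow the spread. At 5%, even the unfavourable case leaves 88.7%. In addition, the analysis is by intention to treat and 168 are to be included. If all 84 per group are analysed, case B unadjusted power is 94%, 93% or 91%. The stated interest in radical resections leaves that analysis set unclear. Both points limit the size of the concern.

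A further objection is that a generic sentence in a condensed article does not exclude a centre term in the full plan. That is true, but the method actually named, in both sections, is unadjusted.

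Three stronger readings may tempt a reader:

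- **The planning mean comes from one hospital** ("the current average lymph node yield at the VU University Medical Center ((VUmc) Amsterdam) is around 20"), so the spread was understated. The mean does not enter a sample size for a difference and does not affect the error term. It is used only to argue that 16 nodes would be acceptable.
- **Chance imbalance within centres biases the comparison.** It costs precision. Under allocation ignoring centre, the unadjusted standard error already reflects it.
- **Allocation ignores centre.** The article says only that "Randomization occurs via an online module"; strata and blocks may be left to the full protocol. That silence supports neither a finding nor a demand to change the randomization.

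**Conclusion.** The point holds as one of efficiency. The stated analysis leaves any between-centre variation in node yield in the error term, and a model with a centre factor is the better method. Whether this is a shortfall or a forgone gain cannot be settled from the article, because the SD and its source are not stated.

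At 66 per group and assumed centre shares of 5% to 20%, power is 1 to 7 points below plan if 7.8 is a within-centre SD. If 7.8 is a total SD, power is as planned, and adjustment would add about 1 to 5 points with arms balanced within centre, or about 0 to 3 without balance. The documents do not support saying that the trial is underpowered, that the comparison is biased or that the false-positive rate is raised.

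**What to change.** Name the primary analysis of node yield as a linear model with treatment and centre as factors, and compare the lower one-sided 95% confidence limit of the treatment coefficient (minimally invasive minus open) with −4. This also gives an explicit bound to set against the margin. In the same place, state the SD used, its source, and whether it includes between-centre variation.

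The cost is a line or two of text and about 7 degrees of freedom. With arms balanced within centre, that alone changes power by less than 0.1 point. If centres hardly differ and allocation is not balanced by centre, the model could lose up to about 1 to 2 points. No change to the sample size or the randomization follows from this point.
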